## Methods/Design

### Study design

ATHENA (Clinicaltrials.gov: NCT01843348; EUDRACT number: 2011-005238-21) is a 12-month, multicentre, randomised, international, prospective, controlled, open-label study with three parallel treatment groups in de novo kidney transplant recipients receiving renal allografts from deceased or living donors (protocol version 3, 29 July 2014). Eligible patients are randomised before transplantation using a validated system to ensure an unbiased treatment assignment in a 1:1:1 ratio to receive either everolimus with a reduced dose of cyclosporine, or everolimus with tacrolimus, or a standard regimen of mycophenolic acid with tacrolimus (Fig. 1). All patients receive induction therapy with basiliximab and maintenance steroids. At the time of randomisation, patients are stratified based on the donor type (living donor, deceased standard criteria donor, or deceased expanded criteria donor) and the participation of the recipient in the European Senior Program. The study protocol and the proposed informed consent form were reviewed and approved by the national institutional review boards or independent ethics committees at each centre and the federal institute for drugs and medical devices (Additional file 1). Written informed consent was obtained from all patients. The clinical study was designed and is conducted in accordance with the ethical principles laid down in the Declaration of Helsinki.

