### Study objectives

The primary objective at month 12 post transplantation is to demonstrate non-inferiority in renal function assessed by the glomerular filtration rate (Nankivell formula) [41] in at least one of the everolimus treatment regimens compared with the standard treatment group receiving mycophenolic acid and tacrolimus. The key secondary objective at month 12 is to evaluate the incidence of treatment failure defined as biopsy-proven acute rejection (BPAR), graft loss, or death among the treatment groups. Other objectives include assessment of individual components of treatment failure, incidence and severity of viral infections (cytomegalovirus (CMV), BK-virus (BKV)), incidence and duration of delayed graft function (DGF), incidence of indication biopsies, incidence of slow graft function, incidence of wound healing complications, and duration of healing. Incidence of viral infections (CMV and BKV) and changes to the viral load are closely monitored throughout the study. In addition, a patient subgroup analysis of CMV-specific T-cells and NK-cells is conducted in a central laboratory. Overall, the safety objectives include assessment of adverse events (AEs) and serious AEs (SAEs), infections and discontinuations due to AEs, and laboratory abnormalities. Exploratory objectives include evaluation of the incidence of HLA-antibodies and among those DSA and non-HLA antibodies (AT_1_R, ET_A_R) by treatment group and its association with acute rejection. HLA-antibodies including DSA were analysed using single antigen Luminex technology at baseline and month 12. In addition, left ventricular (LV) changes are measured by LV hypertrophy (LVH) assessment by echocardiography measurements. Detailed objectives of the study are outlined in Table 3.

**Table 3 Tab3:** Objectives of the ATHENA study

Primary objective	
•	To demonstrate non-inferiority in renal function (estimated GFR by the Nankivell formula) in at least one of the everolimus arms compared with the standard regimen at month 12 post transplantation
Key secondary objectives	
•	To assess the incidence of treatment failure (composite of biopsy-proven acute rejection, graft loss, or death) at month 12 post transplantation
Other secondary objectives	
To evaluate the following:	
•	GFR by different formulae (CKD-EPI, Cockcroft-Gault and MDRD)
•	Incidence of individual efficacy endpoints: biopsy-proven acute rejection, graft loss, and death
•	Incidence and severity of viral infections (CMV, BKV)

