### Statistical analysis

The primary efficacy variable, i.e., renal function at month 12 after randomisation between the treatment groups will be compared with the analysis of covariance (ANCOVA) model, using the treatment and centre as factors, and the estimated glomerular filtration rate at baseline as a covariate. Missing estimated glomerular filtration values will be handled within the ANCOVA analysis by multiple imputations by the last available post-baseline observation carried forward (LOCF) approach. Assuming a common dropout rate of 20 %, a sample size of 612 patients (204 patients in each treatment arm) is required in the study, so as to have at least 80 % power to demonstrate non-inferiority (2.5 % margin, one-sided *t* test) for the primary endpoint.

The primary analysis is based on the full analysis set that consists of all patients who receive at least one dose of the study drug. The per-protocol set includes all patients in the full analysis set who do not have any major deviations from the protocol procedures that may impact the study outcomes. The safety set consists of all patients who receive at least one dose of the study drug and had at least one post-baseline safety assessment.

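### The only printed non-inferiority margin, 2.5 %, has no GFR unit or reference value and is most likely the one-sided significance level mislabelled

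*Protocol article*

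**What the plan says.** All of the following is in the protocol article.

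- **Objective (Study objectives; Table 3).** At month 12 the trial is "to demonstrate non-inferiority in renal function assessed by the glomerular filtration rate (Nankivell formula"), for at least one everolimus arm against mycophenolic acid with tacrolimus.
- **Analysis (Statistical analysis).** The groups "will be compared with the analysis of covariance (ANCOVA) model, using the treatment and centre as factors", with baseline estimated GFR as covariate. The treatment effect is therefore a difference in mean GFR.
- **Sample size (Statistical analysis).** The text reads "Assuming a common dropout rate of 20" %, then "a sample size of 612 patients (204 patients in each treatment arm) is required in the study". The aim is at least 80 % "power to demonstrate non-inferiority", with the conditions given in brackets as 2.5 % "margin, one-sided *t* test) for the primary endpoint".

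No other non-inferiority margin for ATHENA, no significance level, no SD and no assumed true difference is printed anywhere in the article.

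**The concern.** A non-inferiority margin for a mean difference in GFR has to be an amount of GFR, or a percentage of a named reference such as the control mean. The article gives neither. Yet 2.5 % is exactly the usual one-sided significance level, and no significance level appears elsewhere in the sentence. The natural explanation is that alpha was written where the margin belonged.

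This goes beyond a detail left to the full protocol. The article does state a margin, and the figure it states does not suit the endpoint. At stake is the public record of the primary success criterion. The possible readings run from a permitted loss of about 1.25 mL/min to nearly 8 mL/min. A reader who takes the text literally would think the test several times stricter than the one 612 patients would ordinarily support.

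**Working it through.** **Inputs from the article.** 204 per arm, 612 in total, 20 % dropout, at least 80 % power, one-sided *t* test, allocation 1:1:1.

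**Inputs that are assumptions.**
- One-sided alpha of 0.025 and a true difference of zero, unless stated otherwise.
- Control mean of 50–70 mL/min. Reported GFR values in Table 1 lie roughly between 48 and 75, but they mix formulas, time points, means and medians.
- SD of 14–25 mL/min. The lower part can be back-calculated from Table 1 as SD = difference / (z × √(2/n)), assuming two equal arms with all patients analysed:
  - B156, month 12: 7.4 / (2.697 × √(2/55.5)) = 14.5
  - B156, month 6: 8.6 / (2.612 × √(2/55.5)) = 17.3
  - US09: 2.8 / (0.729 × √(2/46)) = 18.4
  - CERTES/LATAM: 4.7 / (2.185 × √(2/85)) = 14.0

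  So Table 1 suggests about 14–18.4. Values of 20–25 are a wider allowance without direct support in the article.

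**Step 1: the plan's own figure.** 204 × 0.8 = 163 evaluable per arm; 163 / 0.8 = 204; 3 × 204 = 612. The dropout step reproduces. The 163 itself cannot be reproduced, because no SD and no margin in GFR units are given.

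**Step 2: 2.5 % as a relative margin.** 0.025 × 50 = 1.25 and 0.025 × 70 = 1.75 mL/min. The standard error of the difference is SD × √(2/163) = 0.1108 × SD. Power comes from the noncentral *t* distribution with 324 degrees of freedom and noncentrality margin / (0.1108 × SD).

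| SD | Power, margin 1.25 | 1.50 | 1.75 |
|---|---|---|---|
| 14 | 12 % | 16 % | 20 % |
| 15 | 11 % | 15 % | 18 % |
| 20 | 8 % | 10 % | 12 % |
| 25 | 7 % | 8 % | 9 % |

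For 80 % power the SD would have to be 4.0–5.6 mL/min. To bring an SD of 14 down to 5.6, baseline adjustment would have to explain 1 − (5.6/14)² = 84 % of the variance.

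**Step 3: 2.5 as mL/min.** Power is 36 % at SD 14, 32 % at SD 15, 20 % at SD 20 and 15 % at SD 25.

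**Step 4: 2.5 % as one-sided alpha.** The margin that 163 per arm can test with 80 % power is, by normal approximation, (1.960 + 0.842) × √(2/163) = 0.310 SD; the noncentral *t* gives 0.311 SD. In mL/min:

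- SD 14: 0.311 × 14 = 4.4
- SD 20: 0.311 × 20 = 6.2
- SD 25: 0.311 × 25 = 7.8

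**Step 5: dropping the zero-difference assumption.** With a literal 2.5 % margin, 80 % power needs margin + true advantage = 0.311 SD.

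- Smallest case (SD 14, margin 1.75): 4.36 − 1.75 = 2.6 mL/min.
- Largest case at SD 20 (margin 1.25): 6.23 − 1.25 = 5.0 mL/min.

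**The case against.** **The power shortfall depends on assuming equal means.** A reader might infer from Step 2 that the printed margin and the printed power are incompatible. The documents do not support that. The article states no assumed difference, its Background argues that lower calcineurin-inhibitor exposure can improve renal function, and Table 1 lists GFR gains of 4.9, 5.3 and 9.8 mL/min (some per 1.73 m²) for other regimens. An assumed advantage of 2.6–5.0 mL/min would rescue the literal reading. This objection stands, although nothing in the article says that such an advantage was assumed.

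**The sample size may be perfectly sound.** If 2.5 % is alpha, 204 per arm is a sensible number for a margin near 0.31 SD. A reader might infer that 612 patients or the 80 % is wrong, but the working does not show this. It shows only that the power cannot be derived from what is printed.

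**A full protocol exists.** The Study design section cites protocol version 3, reviewed by ethics committees and the federal institute. A reader might infer that the margin is still open and could be chosen after the data are seen. A mislabelled figure in an article is no evidence that the approved protocol lacks a margin. Likewise, the absence of an SD or a decision rule from the article is not a fault in itself.

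**The implied margin is per comparison.** The objective needs only one everolimus arm to succeed. If the 80 % refers to at least one success, with both true differences zero and a correlation of 0.5 from the shared control, the implied margin falls to about 0.26 SD with each test at 0.025, or 0.29 SD at 0.0125. That shifts Step 4 modestly and does not make the printed figure a margin.

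What none of this answers is that the text attaches the word margin to a percentage with no reference, and nothing elsewhere in the article corrects it.

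**Conclusion.** The point holds as a wrong statement of the primary decision threshold. The single margin printed cannot be applied to a mean GFR difference as written, and it is most likely the one-sided alpha.

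Taken literally as a relative margin, it gives about 7–20 % power (163 per arm, one-sided alpha 0.025, true difference zero, control mean 50–70, SD 14–25), unless an unstated everolimus advantage of about 2.6–5.0 mL/min (SD 14–20) was built in. Taken as alpha, the design is coherent and corresponds to a margin of about 0.31 SD per comparison, some 4.4–7.8 mL/min for SD 14–25. That margin is not in the text.

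The means and SDs are assumptions, so these figures show the scale of the discrepancy and are not estimates of the trial's true power. That alpha was mislabelled is also an inference, which only the sponsor's own calculation can confirm.

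**What to change.** Correct the sample-size sentence from the sponsor's own calculation:

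- give the protocol's actual margin in absolute GFR units (Nankivell, month 12);
- label 2.5 % as the one-sided significance level, if that is what it is;
- add the SD and the assumed true difference behind the 80 %.

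If 2.5 % really was the margin, name the value it is a percentage of and restate the power from the sponsor's SD and assumed difference. The illustrative powers above should not be put on record in their place, because they rest on assumed inputs.

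The cost is one corrected sentence. No extra patients and no change to the conduct of the trial are needed. The margin may look less strict, or the stated power less favourable, once the right figures are printed.

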## Discussion

ATHENA is one of the largest European multicentre kidney transplant studies. It is the first study evaluating the non-inferiority of renal function as a primary objective in a de novo everolimus-based immunosuppressive protocol, and will determine whether an everolimus-based regimen can preserve renal function versus the current standard of care. The study will also provide insights into the evolution of HLA and non-HLA antibodies, occurrence of viral infections post transplantation, surveillance of cardiovascular comorbidities, and the incidence of wound healing complications [51]. In addition, the trial explores a regimen of everolimus with reduced-dose cyclosporine while the dose of tacrolimus in the everolimus arm and the standard arm is the same. These unique features will further enable the study to provide a direct comparison between the two arms, which will in turn help in optimising the immunosuppressive protocols. As the study addresses a wide range of issues that clinicians face today, its results are awaited with interest.

### Trial status

The study is currently ongoing and actively recruiting patients across 27 sites, 15 centres in Germany and 12 centres in France. The study is expected to be complete by March 2016.

## Abbreviations

AEs: adverse events
ANCOVA: analysis of covariance
BPAR: biopsy-proven acute rejection
C0: trough levels
cGFR: calculated glomerular filtration rate
CKD-EPI: Chronic Kidney Disease Epidemiology Collaboration
CMV: cytomegalovirus
CNI: calcineurin inhibitors
CrCl: creatinine clearance
CsA: cyclosporine
DGF: delayed graft function
DSA: donor-specific antibody
EC-MPS: enteric-coated mycophenolate sodium
eGFR: estimated glomerular filtration rate
EVR: everolimus
HLA: human leukocyte antigen
LV: left ventricular
LVH: left ventricular hypertrophy
MDRD: modification of diet in renal disease
mGFR: measured glomerular filtration rate
MMF: mycophenolate mofetil
MPA: mycophenolic acid
NODM: new-onset diabetes mellitus
NS: not significant
SAE: serious adverse events
